## STUDY SCHEDULE

**Table 1: Summary flowchart**

| Study Periods →                                                                             | Screening and Enrollment                                     | Treatment Period                                                                               | Follow-up until 60 months after enrollment                                                                                                   |
|---------------------------------------------------------------------------------------------|--------------------------------------------------------------|------------------------------------------------------------------------------------------------|----------------------------------------------------------------------------------------------------------------------------------------------|
| Time unit →                                                                                 | Days                                                         | Weeks                                                                                          | Months                                                                                                                                       |
| Patient Information and Informed Consent                                                    | -28 – 0                                                      |                                                                                                |                                                                                                                                              |
| Medical history and demographics                                                            | -28 – 0                                                      |                                                                                                |                                                                                                                                              |
| Panendoscopy, assessment of exposure and staging according to institutional local standards | -28 – 0                                                      |                                                                                                |                                                                                                                                              |
| Eligibility Criteria Check                                                                  | -28 – 0                                                      |                                                                                                |                                                                                                                                              |
| SCCGL-oriented physical examination                                                         | -28 – 0                                                      |                                                                                                |                                                                                                                                              |
| VHI # , RBH, GNE, SPR, JS                                                        | -28 – 0                                                      |                                                                                                | (1.5) # , 6, 12, 18, 24 (+/-15 days)                                                                                              |
| Enrollment and randomization*                                                               | 0                                                            |                                                                                                |                                                                                                                                              |
| Endoscopic assessment of the index tumor, symptom oriented physical examination             | -28 – 0                                                      |                                                                                                | every 3 months (+/-15 days) until 24 th month
every 6 months (+/-15 days) between 24 th and 60 th months |
| Evaluation of actual smoking status and toxicity according to CTCAE v.5.0 (Appendix A)      | -28 – 0 (baseline smoking status and toxicity ‡ ) | weekly during radiotherapy and within one week of surgery: no need to document except for SAEs |                                                                                                                                              |
| Pregnancy test for women with child-bearing potential                                       | -28 – 0                                                      | 3 – 7 ‡                                                                             | until 3 rd month ‡                                                                                                     |
| Arm A: Transoral CO 2 -Laser Microsurgical Cordectomy ▽               |                                                              | day of surgery +/- day of re-resection                                                         |                                                                                                                                              |
| Arm B: Single Vocal Cord Irradiation ▽                                           |                                                              | 3 (16 fractions)                                                                               |                                                                                                                                              |

GNE: Glottal-to-Noise Excitation Ratio; JS: Jitter and Shimmer; RBH: Roughness – Breathiness – Hoarseness; SAEs: serious adverse events; SCCGL: squamous cell carcinoma of glottic larynx; SPR: Singing Power Ratio; VHI: voice handicap index

\*: Even if done on the same day, patient enrollment shall be done after the completion of the necessary documentation

#: VHI at 6 weeks after the end of treatment (regardless of study arm) will be assessed to evaluate the need for phoniatric rehabilitation, but not as a study-specific outcome measure (i.e. primary endpoint) to avoid lead time bias. Patients with a VHI > 14 will be recommended to undergo a phoniatric rehabilitation, but the examiner should not try to persuade the patient. Similarly, any VHI >14 at any follow-up time point or patients' request justifies the need for phoniatric rehabilitation, which will be recommended to the patients regardless of study arm. No need to record the VHI in the CRFs.

‡: The baseline toxicity scores and smoking status may be documented after the accrual but it must be done before the start of trial treatment.

‡: If clinically indicated

▽: The treatment shall start within 28 days post-accrual

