## **5. STUDY OUTCOMES**

### **5.1 Primary Outcome**

- Average of the VHI assessed at 6, 12, 18, and 24 months

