### 9.2.1 Assessment of primary outcome

The VHI allows the person in question to make a subjective assessment of their own vocal problem. It is a questionnaire with 30 items (will be provided in different languages apart from the protocol). Using this questionnaire, the affected people can describe the degree to which their voice restricts their everyday life. The higher the score (0-120), the greater is their subjectively experienced handicap (score 0-14 = no; 15-28 = mild; 29-50 = moderate; 51-120 = severe handicap). The freeware open-source software DigitalVHI by Christian Herbst will be used to record the VHI by each visit. DigitalVHI only generates pdf reports per VHI assessments and does not store any data locally or on a server.

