## **11.4 Handling of missing data and drop-outs**

We expect that all randomized patients have complete baseline data. All patients that have at least one outcome assessment can be considered in repeated-measures analyses. Models will implicitly correct for missing data based on the missing at random mechanism. If there are patients with no outcome data at all, we will perform multiple imputation. Details will be described in the SAP. For the time-to-event analysis, patient drop-outs will be accounted for by censoring.

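### The 6-week VHI is measured in both arms but its CRF entry is waived, so the most direct auxiliary for the planned imputation would not be in the analysis database

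*Protocol*

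**What the plan says.** The footnote to Table 1 (Study Schedule, repeated in section 9.1) states "VHI at 6 weeks after the end of treatment (regardless of study arm) will be assessed to evaluate the need for phoniatric rehabilitation". It excludes this score from the outcomes and gives lead time bias as the reason. A score above 14, at this or any later visit, leads to a recommendation of rehabilitation. The footnote closes with "No need to record the VHI in the CRFs".

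The VHI row of Table 1 lists baseline, a bracketed 1.5-month assessment, and then months 6, 12, 18 and 24. Section 5.1 defines the primary outcome as "Average of the VHI assessed at 6, 12, 18, and 24 months", so the 6-week score plays no part in it.

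On missing data, section 11.4 says "Models will implicitly correct for missing data based on the missing at random mechanism" and "If there are patients with no outcome data at all, we will perform multiple imputation", with details left to the SAP.

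Three other places bear on whether the score could be used:
- Section 9.2.1: "DigitalVHI only generates pdf reports per VHI assessments and does not store any data locally or on a server".
- Section 12.2.4: the data for the final analysis are taken from the study database.
- Section 9.2.4: the last examination after withdrawal for an adverse event concerns toxicity and names no VHI.

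**The concern.** The protocol collects a post-treatment value of the primary instrument and then does not ask for it to be stored where the analysis could use it. The patients for whom section 11.4 plans multiple imputation are those with no VHI at months 6 to 24. Some of them will have completed the 6-week questionnaire. If early loss is related to a poor voice soon after treatment, the 6-week score is what would make a missing-at-random assumption more credible for these patients.

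This cannot be left to the SAP. The SAP can choose among stored variables, but it cannot use one that was never entered. Data capture is fixed in the protocol and the eCRF.

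The score also triggers a recommendation that may itself affect later VHI. The protocol does not ask for uptake of rehabilitation to be recorded.

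**Working it through.** **1. Who is affected.** Setting the schedule beside section 11.4:

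| Pattern | Handling under 11.4 | Would a stored 6-week VHI help? |
|---|---|---|
| At least one VHI at months 6–24 | Stays in the mixed model | Little |
| Attends week 6, no VHI from month 6 on | Multiple imputation | Yes: only scheduled post-treatment VHI |
| Leaves before week 6 | Multiple imputation | No: it does not exist |

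The point concerns the middle row only.

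**2. The plan's own figure.** Inputs from section 11.1: difference 8, SD 8, two-sided alpha 0.05, power 80%. The normal approximation gives 16 per arm. The exact two-sample t-test gives power 78.1% at 16 per arm and 80.7% at 17, so 17 per arm (34 in total) is reproduced. Section 11.1 adds no allowance for dropout.

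**3. Precision.** Suppose m of 17 per arm are lost after week 6, f = m/17, and the 6-week VHI has correlation ρ with the 6–24 month average given baseline. Both f and ρ are assumptions. With the score as auxiliary, the effective number per arm is approximately

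n_eff = (17 − m) / (1 − ρ²f).

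Example: m = 3, ρ = 0.7 gives 14 / (1 − 0.49 × 0.176) = 15.33.

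| Lost per arm | Power without 6-week VHI | Power with it, ρ = 0.3 to 0.7 |
|---|---|---|
| 1 | 78.1% | 78.4% to 79.4% |
| 2 | 75.3% | 75.8% to 77.9% |
| 3 | 72.1% | 72.9% to 76.3% |

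The recovery is about 0.3 to 4 percentage points.

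**4. Bias, by direct arithmetic.** Suppose the loss is in one arm only, the lost patients' 6-week VHI is D points worse, and the slope of later VHI on 6-week VHI is b. Then the bias in that arm's mean is f × D × b.

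- Smallest case: 1/17 × 8 × 0.3 = 0.14 points.
- Middle case: 2/17 × 16 × 0.5 = 0.94 points.
- Largest case: 3/17 × 16 × 0.7 = 1.98 points.

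**5. Bias, by simulation.** The set-up was 4,000 trials of 17 per arm, SD 8, correlation with later VHI of 0.4 for baseline and 0.6 for the 6-week score, and about 20% loss in one arm driven by the 6-week score. ANCOVA on observed patients with baseline only had bias 0.80. Imputation that included the 6-week score had bias −0.01. The empirical SD was 2.3 in both. As a share of the target, 0.80/8 = 10%.

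Other assumptions move this figure:
- Varying the dropout slope at 20% loss gives about 0.6 to 0.95 points.
- At 10% loss it is 0.3 to 0.5 points, falling to 0.0 to 0.2 when the 6-week correlation is 0.3 to 0.4.
- With a single patient lost it is 0.2 to 0.4 points.

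On total error the gain is smaller. In the 20% case, root mean squared error falls from √(2.3² + 0.8²) = 2.44 to 2.30.

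The baseline-only comparator is a complete-case analysis, not the imputation planned in 11.4. An imputation using only arm and baseline should behave much like it. One that also used surgical and safety data might do somewhat better.

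**The case against.** The strongest reply is that nothing is contradicted. The 6-week VHI is a screen for rehabilitation, it is kept out of the endpoints for a stated reason, and no planned analysis needs it. That is fair, and it keeps the point minor. It does not explain the waiver: lead time bias is a reason not to average the score into the outcome, and an imputation auxiliary leaves the outcome unchanged.

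Several stronger readings are tempting and are not supported:

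- *The protocol forbids recording, or throws the value away.* It only says that recording is unnecessary, and a pdf is generated at each assessment, so a source record may exist.
- *The imputation would have only pre-treatment information.* Before month 6 the protocol also collects cordectomy type, margins and re-resection (8.2.2 to 8.2.3), 30-day surgical complications (8.2.5), and grade 3 or higher events as SAEs (9.2.3), which could include severe hoarseness (Appendix A). Grade 1–2 events before the month-6 visit need not be reported, so these data are coarser than a VHI, but they exist.
- *Changing treatment makes the VHI missing.* Patients taken off treatment move to follow-up (7.5) and are analysed as randomized (11.3.1).
- *The waiver covers the primary-endpoint visits.* The footnote mark does sit on the row label as well as on the 1.5-month entry, and the last sentence is unqualified. But section 5.1 makes the month 6–24 scores the primary outcome, section 12.1.1 requires requested CRF data to be recorded, and section 12.2.5 provides for central review of the primary outcome data. At most the wording deserves tidying.

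**Conclusion.** The point holds as a minor, inexpensive improvement. As written, the 6-week VHI would not be in the analysis database. For patients lost between week 6 and month 6 it is the only scheduled post-treatment VHI and the best single auxiliary for the imputation in 11.4. The lead-time argument justifies its exclusion from the primary average only.

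The size is conditional. With little early loss the gain is near zero. In an assumed unfavourable case (20% loss in one arm, driven by the 6-week score, correlation 0.6) it avoids about 0.8 VHI points of bias against a target of 8. The most extreme arithmetic case above reaches about 2 points. A reader might take 0.8 as the bias to expect; the documents do not support that, because they give neither a dropout rate nor a correlation, and 20% of 17 is about 3.4 patients lost in one arm and none in the other. The sample size and the primary outcome definition are not affected.

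**What to change.** In both copies of the Table 1 footnote, replace the waiver with an instruction to enter two items in the eCRF as non-endpoint variables: the 6-week VHI, and whether phoniatric rehabilitation was taken up. State that the 6-week VHI will be used only as an auxiliary variable in the multiple imputation of section 11.4, and leave the primary outcome in section 5.1 as it is. In the same edit, add a few words making clear that all month 6, 12, 18 and 24 VHI scores must be recorded.

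The cost is one or two data-entry fields for each of 34 patients, for a questionnaire that is already completed. No visit, assessment or clinical rule changes.

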## **2. ETHICAL AND REGULATORY ASPECTS**

The decision of the CEC concerning the conduct of the study will be made in writing to the Sponsor-Investigator before commencement of this study. The clinical study can only begin once approval from all required authorities has been received. Any additional requirements imposed by the authorities shall be implemented.

### **2.1 Study registration**

The study will be listed in [clinicaltrials.gov](https://clinicaltrials.gov) and in the Swiss National Clinical Trials Portal.

### **2.2 Categorization of study**

Category A: the treatments involved in the study are not experimental and being used as two distinct standards of care.

### **2.3 Competent Ethics Committee (CEC)**

The responsible investigator at each site ensures that approval from an appropriately constituted CEC is sought for the clinical study.

Approval from all involved CECs is required prior to the start of the study. No changes to the protocol will be made without prior approval from the CECs, except if necessary to eliminate immediate hazards to participants. Premature study end or interruption of the study is reported within 15 days. The regular end of the study is reported to the lead CEC within 90 days, the final study report shall be submitted within one year after study end. Amendments are reported according to chapter 2.10.

### **2.4 Competent Authorities (CA)**

The regular end of the study is reported to the CEC within 90 days, the final study report shall be submitted within one year after study end. Amendments are reported according to chapter 2.10, except for non-substantial amendments that are reported as soon as possible.

### **2.5 Ethical Conduct of the Study**

The study will be carried out in accordance to the protocol and with principles enunciated in the current version of the Declaration of Helsinki, the guidelines of Good Clinical Practice (GCP) issued by ICH, the Swiss Law and Swiss regulatory authority's requirements. The CEC and regulatory authorities will receive annual safety and interim reports and be informed about study stop/end in agreement with local requirements.

### **2.6 Declaration of interest**

The investigators declare that they have no conflict of interest.

### **2.7 Patient Information and Informed Consent**

The investigators will explain to each participant the nature of the study, its purpose, the procedures involved, the expected duration, the potential risks and benefits and any discomfort it may entail. Each participant will be informed that the participation in the study is voluntary and that he/she may withdraw from the study at any time and that withdrawal of consent will not affect his/her subsequent medical assistance and treatment.

The participant will be informed that his/her medical records may be examined by authorized individuals other than their treating physician.

All participants for the study will be provided a participant information sheet and a consent form describing the study and providing sufficient information for participant to make an informed decision about their participation in the study.

The patient information sheet and the consent form will be submitted to the CEC to be reviewed and approved. The formal consent of a participant, using the approved consent form, must be obtained before the participant is submitted to any study procedure.

The participant should read and consider the statement for at least 24 hours before signing and dating the informed consent form and should be given a copy of the signed document. The consent form must

also be signed and dated by the investigator (or his designee) and it will be retained as part of the study records.

## **2.8 Participant privacy and confidentiality**

The investigators affirm and uphold the principle of the participant's right to privacy and that they shall comply with applicable privacy laws. Especially, anonymity of the participants shall be guaranteed when presenting the data at scientific meetings or publishing them in scientific journals.

Individual subject medical information obtained as a result of this study is considered confidential and disclosure to third parties is prohibited. Subject confidentiality will be further ensured by utilizing subject identification code numbers to correspond to treatment data in the computer files.

For data verification purposes, authorized representatives a competent authority or the CEC may require direct access to parts of the medical records relevant to the study, including participants' medical history.

## **2.9 Early termination of the study**

The Sponsor-Investigator may terminate the study prematurely according to certain circumstances, for example:

- ethical concerns,
- insufficient participant recruitment,
- when the safety of the participants is doubtful or at risk, respectively,
- alterations in accepted clinical practice that make the continuation of a clinical trial unwise,
- early evidence of benefit or harm of the experimental intervention

## **2.10 Protocol amendments**

Substantial amendments are only implemented after approval of the CEC and CA respectively.

Under emergency circumstances, deviations from the protocol to protect the rights, safety and well-being of human subjects may proceed without prior approval of the sponsor and the CEC/CA. Such deviations shall be documented and reported to the sponsor and the CEC/CA as soon as possible.

All Non-substantial amendments are communicated to the CA as soon as possible if applicable and to the CEC within the Annual Safety Report (ASR).

### 3. BACKGROUND AND RATIONALE

#### 3.1 Background and Rationale

Head and neck squamous cell carcinoma (HNSCC) is the 6th most common type of cancer worldwide. Of all head and neck cancers, approximately 30% originates from the larynx. In Europe, annually 52,000 patients are diagnosed with cancer of the larynx. About 50–60% of laryngeal squamous cell carcinomas arise from the glottic region and over 80% of these patients present in an early stage. The larynx has important roles in production of voice, coordination of deglutition, and respiration. Therefore, the treatment aim of laryngeal cancer is not only achievement of maximum disease control, but also maintenance of function. Transoral CO2-Laser Microsurgical Cordectomy (TLM) and radiotherapy are well-established standard treatment modalities for unilateral stage 0-I carcinoma in situ and squamous cell carcinoma of glottic larynx (for convenience, both will be mentioned as SCCGL throughout this protocol). Based on various clinical studies and meta-analyses, functional and oncological outcome (overall survival and local control) after both treatment modalities are comparable. However, no properly conducted randomized trials comparing these treatments exist. The only such trial with the endpoint of voice quality had to be prematurely closed due to low accrual.

The treatment option varies remarkably in different countries and among institutions. Especially in the case of unilateral SCCGL, other factors such as voice quality, cultural and socio-economic factors, and patients' preference should be considered. Hoarseness is one of the main and early signs of SCCGL, whereas both radiotherapy and TLM influence voice quality by altering the vocal cord motion and anatomy. Another issue worth to consider is the treatment time. Surgery is performed in one day followed by a few days of hospital stay. In contrast, radiotherapy is applied in daily fractions. Although each fraction only takes few minutes, the patients have to visit the radiation oncology department over a course of 4 to 7 weeks, depending on the institutional preference of dose and fractionation. The post-treatment follow-up schedules are identical for both strategies.

The differences between both treatment modalities have been extensively reported. However, either due to no meaningful difference or due to the heterogeneity in the voice analysis techniques, several studies revealed no significant differences while better voice quality was reported after radiotherapy as compared with TLM in other studies.

The traditional radiotherapy involves the treatment of the whole larynx over a period of 4 to 7 weeks. Recently, a new radiotherapy technique was introduced by a team of researchers from Netherlands, where the treated target volume consists of involved vocal cord and therefore 8 to 10 fold smaller than the target volumes used for traditional whole larynx irradiation. The treatment is reduced to 16 fractions with higher dose per fraction which corresponds to 3 weeks and a day. The results of a prospective cohort (n=30) with single vocal cord irradiation (SVCI) were compared with the results of a historical prospective cohort (n=131) previously treated with whole larynx radiotherapy in the same institute. The median follow-up was 30 months. The voice handicap index (VHI) at all time points beginning from the 6th week after SVCI was significantly superior to the same time points with conventional radiotherapy. Moreover, a comparable local control with SVCI (100%) vs. conventional radiotherapy (92%) was reported at two years, p=0.24. Based on that, the SVCI technique was implemented as a standard approach for SCCGL in many radiation oncology clinics in the recent years, including the centers participating in this clinical trial.

In conclusion, the long-term voice quality and oncologic outcome (survival and local tumor control) are comparable with both TLM and traditional radiotherapy. Furthermore, the new SVCI technique offers a possibly superior long-term voice quality with an at least equal oncologic outcome compared to traditional radiotherapy. With this background, our main aim is to compare SVCI to TLM with the main focus of patient-reported voice quality.

